## Abstract

**Background:**

Allergic rhinitis is one of the most common health complaints worldwide. Complementary and alternative medical approaches have been employed to relieve allergic rhinitis symptoms and to avoid the side effects of conventional medication. Acupuncture has been widely used to treat patients with allergic rhinitis, but the available evidence of its effectiveness is insufficient. Our objective is to evaluate the effectiveness of acupuncture in patients in Korea and China with persistent allergic rhinitis compared to sham acupuncture treatment or waitlist control.

**Methods:**

This study consists of a multi-centre (two centres in Korea and two centres in China), randomised, controlled trial with three parallel arms (active acupuncture, sham acupuncture, and waitlist group). The active acupuncture and sham acupuncture groups will receive real or sham acupuncture treatment, respectively, three times per week for a total of 12 sessions over four weeks. Post-treatment follow-up will be performed a month later to complement these 12 acupuncture sessions. Participants in the waitlist group will not receive real or sham acupuncture treatments during this period but will only be required to keep recording their symptoms in a daily diary. After four weeks, the same treatment given to the active acupuncture group will be provided to the waitlist group.

**Discussion:**

This trial will provide evidence for the effectiveness of acupuncture as a treatment for persistent allergic rhinitis. The primary outcome between groups is a change in the self-reported total nasal symptom score (i.e., nasal obstruction, rhinorrhea, sneezing, and itching) from baseline at the fourth week. Secondary outcome measures include the Rhinitis Quality of Life Questionnaire score and total non-nasal symptom score (i.e., headache, itching, pain, eye-dropping). The quantity of conventional relief medication used during the follow-up period is another secondary outcome measure.

**Trial registration:**

Current Controlled Trials ISRCTN90807007

## Background

Allergic rhinitis (AR) is a highly prevalent major chronic respiratory disease. It significantly impacts quality of life (QoL) and creates an economic burden. AR can be classified as intermittent or persistent allergic rhinitis (PER), as described by the recent 'Allergic Rhinitis and its Impact on Asthma (ARIA)' guidelines [1]. The conventional treatment of AR symptoms, such as nasal obstruction, rhinorrhea, sneezing, and itching, includes the use of intranasal corticosteroids, oral anti-histamines with or without decongestants, immunotherapy, and education [2]. Substantial numbers of patients with AR are not satisfied with conventional medical treatment and repeatedly experience side effects. As a result, a large number of patients with AR are turning to complementary and alternative treatments [3,4].

Acupuncture not only produces an anti-nociceptive effect, but also has anti-inflammatory or immunomodulatory effects against chronic inflammatory conditions in humans [5]. The anti-inflammatory action of acupuncture is thought to be mediated by neural immune reflexes [6,7], i.e., the cholinergic anti-inflammatory pathway of the central nervous system [8]. Although firm evidence has not been established, acupuncture has been used by patients with AR. The results of our systematic review of six randomised controlled trials (RCTs) on acupuncture for PER revealed that acupuncture had a favourable effect on AR symptom scores compared to placebo acupuncture (standardised mean difference: 0.45, 95% CI: 0.13 – 0.78) [9]. However, the results of our review on the efficacy of acupuncture in the treatment of AR were inconclusive, consistent with other studies [10,11]. This may be because all relevant RCTs were limited by methodological defects, including inappropriate sample size, inappropriate placebo treatment, missing information, and lack of clarity about the quality of the acupuncture practitioners [12,13]. A deficiency is evident even in a recent, high-quality randomised controlled trial [14] in which acupuncture was used for PER in an eight-week treatment and 12-week follow-up period. The results showed an improvement in the cumulative seven-day scores between the active and sham acupuncture groups. In this study, Xue *et al. *used a shorter needle in the placebo procedure compared to the active acupuncture group. This suggests that their strategy may be flawed with respect to patient blinding. Furthermore, most RCTs for AR allowed the concomitant use of pharmacological medication for symptomatic relief of AR, or acupuncture was compared to conventional medication and not to placebo needle treatment. Success of the blinding procedure has not been assessed in RCTs, apart from one trial [15]. Consequently, the difference in outcomes between the two groups could be unrelated to the effect of acupuncture itself, and may be influenced by the use of over-the-counter (OTC) or conventional medications that yield symptomatic relief. Thus, disallowance of concomitant medications is needed in a randomised controlled trial for PER in order to detect the specific effects of acupuncture.

With these constraints, we planned a rigorous multi-centre randomised controlled trial with a large sample size.

## Method/design

### Objective

The aim of this study is to investigate the effectiveness of acupuncture compared with sham acupuncture or waitlist in patients with moderate to severe PER in Korea and China.

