### Primary outcome

Primary outcome will be the change in the weekly average of total nasal symptom score (TNSS) recorded in participants' diaries between the one-week of run-in period and the 4P^th ^week of the study. This scoring system was previously validated [14,16].

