### Statistical methods

#### Analysis

Analysis will be performed for each of the following groups: 1) an intention-to-treat population consisting of all randomised participants with at least one measurable outcome report following acupuncture treatment (any missing data will be replaced with the last observation values); 2) a protocol-specific population including only participants without major protocol deviations. All data will be analysed descriptively. All main analyses will be based on the intention-to-treat population. For primary and secondary outcome measures, analysis of covariance (ANCOVA) using the differences in the change of outcome variable scores as the dependent variable, baseline outcome variable scores as the covariate, and allocated group and centres as the fixed factors will be performed. To compare the active acupuncture group with the sham acupuncture group and with the waitlist group, a single ANCOVA using dummy variables for the sham and waitlist group (thus coded 0, 0; 1, 0; 0, 1 for the active acupuncture group, sham acupuncture group, and waitlist group, respectively) will be conducted. All adverse events reported during the study will be included in the case report forms; the incidence of adverse events will be calculated. The percentage of subjects with adverse events in each group will be calculated and compared using the chi-squared test or Fisher's exact test.

Statistical analyses will be performed using the SAS statistical package program (ver. 9.1.3, SAS Institute Inc, Cary, NC), and the level of significance will be established at α = 0.05.

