#### Sample size

For power analysis and sample size calculation, we conducted a pilot study with a sample size of 19 (9 in the active acupuncture arm and 10 in the sham acupuncture group). In this study, the pooled SD of TNSS was 4.74 and the mean difference of TNSS change between the active and sham acupuncture group was 2.53. This difference was larger than that of recent successful acupuncture RCT on PER, reported as 1.8 [14]. TNSS reduction in the active acupuncture group in our pilot study was 4.12, higher than the minimal clinically important differences (i.e. 2.2) [22]. Therefore, the result of our pilot study showed the potential of acupuncture treatment and supported the need for the present trial. The SD of the pilot study was adjusted for better application to the true population. In order to achieve this adjustment, we multiplied the SD from the pilot data by a correction factor of 1.148. This adjustment provides a 75% probability that the resulting estimate of SD will be at least as large as the true population SD [23]. For the sample size calculation, we established a sample size (N) for an independent t test using the adjusted SD, and the difference in TNSS change between the active and sham acupuncture group with a power of 80% and alpha value of 2.5% (two-tailed). We then estimated a Pearson correlation value (R) of 0.76 between baseline and the change of TNSS in our pilot study. Finally, we multiplied N by (1-R^2^) to yield the sample size needed for ANCOVA analysis [24]. The results indicated that the number of subjects in the active acupuncture group and in the sham acupuncture group was 38. If we compare the change in TNSS for the active acupuncture group with that of the waitlist group, assuming that pooled SD and R are similar to our pilot study, the differences between groups will be larger, and thus 38 subjects in the waitlist group size will be enough to detect significant differences in the change in TNSS for the active acupuncture group. We applied a 2:2:1 ratio to the active acupuncture group, sham acupuncture group, and waitlist group, respectively, and we expect that this allocation ratio will raise the statistical power. We plan to enrol 95, 95, and 48 participants in the active acupuncture group, sham acupuncture group, and waitlisted group, respectively, allowing for a 20% withdrawal rate.

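### The protocol tests acupuncture against sham and against waitlist but does not say which contrast decides, so a win over the unblinded waitlist alone has no defined conclusion

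*Protocol article*

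**What the plan says.** - **Objective:** "to investigate the effectiveness of acupuncture compared with sham acupuncture or waitlist in patients with moderate to severe PER". The abstract's Background also joins the two controls with *or*: "persistent allergic rhinitis compared to sham acupuncture treatment or waitlist control".
- **Primary outcome:** "Primary outcome will be the change in the weekly average of total nasal symptom score (TNSS) recorded in participants' diaries", from run-in to week 4. No comparator is attached. The abstract's Discussion speaks of a between-group outcome without saying which groups.
- **Analysis:** "To compare the active acupuncture group with the sham acupuncture group and with the waitlist group, a single ANCOVA using dummy variables". The two contrasts have equal standing, and "the level of significance will be established at α = 0.05". No order, split or both-must-win rule is given.
- **Sample size:** the calculation is for "the difference in TNSS change between the active and sham acupuncture group with a power of 80% and alpha value of 2.5% (two-tailed"). The waitlist arm is then argued to be large enough because its difference from active should be larger.
- **Purpose and design:** the main Background says that "disallowance of concomitant medications is needed in a randomised controlled trial for PER in order to detect the specific effects of acupuncture", and the Design section calls the trial subject-blinded and sham-controlled.

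**The concern.** The two contrasts answer different questions. Active against sham isolates the specific effect of needling at the chosen points, which is the purpose given in the Background. Active against waitlist measures specific and non-specific benefit together. Waitlist participants receive no needling and therefore know their arm, and they score their own diary TNSS, so that contrast is not subject-blinded. The protocol itself expects it to show the larger difference.

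A null result against sham with a significant result against waitlist is therefore a realistic outcome. The protocol does not say what would then be concluded about effectiveness, and a choice made after the data are seen would carry little weight.

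**Working it through.** **1. Reproduce the plan's sample size.** Inputs from the Sample size section: pilot SD 4.74, factor 1.148, difference 2.53, R = 0.76, power 80%, two-tailed alpha 2.5%.
- Adjusted SD = 4.74 × 1.148 = 5.44.
- n per group = 2 × [5.44 × (2.241 + 0.842) / 2.53]² = 87.9.
- ANCOVA factor: 1 − 0.76² = 0.4224. 87.9 × 0.4224 = 37.1, rounded up to 38, as stated. (The exact t calculation gives 90 × 0.4224 = 38.0.)
- 2:2:1 around 38 on waitlist gives 76/76/38. Dividing by 0.8 gives 95/95/48, total 238, as stated.
- At two-sided 5% the same calculation gives 31, so the stated 38 depends on the 2.5% level, which is not the 0.05 in the Analysis section.

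**2. Standard errors with 76/76/38 evaluable.**
- Residual SD = 5.44 × √0.4224 = 3.54.
- Active v sham: 3.54 × √(1/76 + 1/76) = 0.574.
- Active v waitlist: 3.54 × √(1/76 + 1/38) = 0.703.
- Correlation through the shared active arm: (1/76) / √[(2/76)(3/76)] = 1/√6 = 0.41.

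**3. Familywise error when all three arms are equal** (bivariate normal, each test two-sided).

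| Level per contrast | At least one significant | If independent |
|---|---|---|
| 5% | 9.3% | 9.75% |
| 2.5% | 4.75% | 4.94% |

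**4. No specific effect, real non-specific effect.** Let active equal sham, and let both beat waitlist by d. The protocol gives no waitlist difference, so d is assumed. The value 1.59 is the pilot sham change implied by 4.12 − 2.53; using it here also assumes no change on waitlist. The values 1.8 and 2.53 are active–sham differences quoted in the Sample size section. Power of the waitlist contrast = Φ(d/0.703 − 1.96).

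| d | Waitlist contrast significant (5%) | At least one contrast favours active (5%) | At least one (2.5% each) |
|---|---|---|---|
| 1.0 | 29.6% | 30.4% | 21.1% |
| 1.59 | 61.9% | 62.0% | 50.9% |
| 1.8 | 72.6% | 72.8% | 62.7% |
| 2.53 | 95.0% | 95.0% | 91.3% |

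The second and third columns are nearly equal, so the chance of any win is almost wholly power for the waitlist difference. Active v sham falsely favours active in 2.5% of trials at two-sided 5%. Subtracting this from the third column leaves a waitlist-only win in about 28%, 60%, 70% and 93% of trials. Moving to 2.5% per contrast lowers these chances but does not remove the outcome.

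**5. Power if active v sham decides.** 2.53/0.574 = 4.41. Φ(4.41 − 1.96) = 99.3% at two-sided 5%; Φ(4.41 − 2.24) = 98.5% at 2.5%.

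**The case against.** The strongest reply is that the article already leans to sham. The Design section labels the trial sham-controlled, the Background wants specific effects, the only computed sample size is active against sham, the waitlist arm gets half the allocation, and the blinding question asks about active or sham. A full protocol or SAP may also set a testing order. One ANCOVA reports both estimates, so a null result against sham would be visible. All this stands, but it shows intent and is not a decision rule. The point does not rest on missing detail alone: the objective as worded gives the two controls equal rank, and the Analysis section tests both at 0.05.

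Two stronger readings are not supported:
- A reader might infer that *or* sets an either-win rule, so that beating waitlist alone counts as success. The aim is only to investigate and contains no success criterion, and the Analysis section compares active with sham *and* with waitlist.
- A reader might take the 30% to 95% as a false-positive rate. In that scenario active truly beats waitlist, so the figures are power at assumed differences. Their like-for-like comparator is the 2.5% favourable error of the sham contrast at two-sided 5%, not 5%.

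The 2.5% in Sample size may be a split over two contrasts, but the article does not say so. If it is, it treats both contrasts as able to decide.

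**Conclusion.** The point holds as an ambiguity in the trial's headline conclusion, and it should be removed before unblinding. Nothing shows that the authors intend to claim effectiveness from waitlist alone, but nothing in the text settles what such a result would mean. Following the Analysis section as written gives about 9.3% familywise error over the two contrasts when all arms are equal. A split to 2.5% each brings this to 4.75% but leaves the interpretation open.

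The figures assume 76/76/38 evaluable, the plan's inflated SD and correlation, a normal approximation, and a two-sided reading of the 0.05. The chance of a significant waitlist contrast also depends on d, which the protocol does not supply. The sample size itself reproduces and is not in dispute.

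**What to change.** 1. In Objective, Primary outcome and Analysis, and in the abstract's Background, name active against sham on week-4 TNSS change as the primary contrast that decides effectiveness.
2. Make active against waitlist the second step, tested formally only if the first is significant. Otherwise report its estimate and 95% CI as overall benefit, specific plus non-specific.
3. State one alpha in Analysis and Sample size. Under the fixed order, two-sided 5% for each step suffices. If 2.5% is kept, say why and use it in both places.

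Requiring both contrasts to succeed would be an alternative with an equally clear conclusion.

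The cost is wording only: planned enrolment is unchanged, and power against sham is about 99% at 5% or 98.5% at 2.5% on the plan's inputs. The sponsor gives up any effectiveness claim based on the waitlist contrast alone. Moving to 5% would also relax the level at which the sample size was derived, and this should be stated openly.

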### Primary outcome

Primary outcome will be the change in the weekly average of total nasal symptom score (TNSS) recorded in participants' diaries between the one-week of run-in period and the 4P^th ^week of the study. This scoring system was previously validated [14,16].

### Secondary outcomes

Secondary outcome measures include the Rhinitis Quality of Life Questionnaire (RQLQ) [17] score and a total non-nasal symptom score (i.e., headache, itching, pain, eye-dropping) [14] after the 12-session/four-week acupuncture treatment period. The quantity of conventional relief medication used during follow-up period (four weeks) will also be recorded.

### Design

A multi-centre (two centres in Korea and two in China), randomised, subject- and assessor-blinded, sham acupuncture controlled trial will be conducted at the Department of Acupuncture and Moxibustion, Kyung-Hee University Medical Centre in Seoul, the Acupuncture and Moxibustion Research Centre of the Korean Institute of Oriental Medicine (KIOM) in Daejeon, the Acupuncture and Moxibustion Clinic of Guang'anmen Hospital, and Dongzhimen Hospital at Beijing. The study will be sequentially conducted as follows: a run-in period of one week prior to randomisation, a treatment period of four weeks (three sessions per week), and a follow-up period of four weeks. The total study period will be nine weeks. At the end of the run-in period, participants will be randomised to the active acupuncture group, the sham acupuncture group, or the waitlist group by a computer-generated random number list (Figure 1).

**Figure 1 F1:**
[figure not shown]
**Study Flow Chart**.

### Eligibility

#### Inclusion criteria

Eligible participants will be those previously diagnosed with moderate to severe PER, according to the ARIA criteria. Patients will be required to complete the baseline AR diary. Written informed consent will be obtained from each participant. Participants ≥ 18 years of age will be recruited from each centre via local newspaper advertisements and posted notices. Since the research involves moderate to severe PER or severe PER [1], the inclusion criteria will include greater than four days/week and greater than four consecutive weeks of symptoms and one or more of the following conditions: sleep disturbance, impairment of daily activities such as sports and/or leisure, impairment of school or work, or troublesome symptoms. All participants will have to show at least one positive result on an allergic skin prick reaction test. A standard panel of antigens will be used, i.e., positive (histamine) and negative (saline) controls, *Dermatophagoides farinae, Dermatophagoides pteronyssinus*, dog fur, cat fur, short ragweed, Orchard grass, Bermuda grass, Mugwort, Hazel, Alternaria tenuis, *Aspergillus fumigatus*, Candida albicans, *Cladosporium herbarum*, Alder, Beech, and cockroach (*Blatella germanica*) (Allergopharma, Germany).

Participants will be instructed to stop PER symptomatic relief medication during the run-in and treatment periods and will be provided the usual care instruction for AR. During the follow-up period, they will be allowed to start relief medication, if required.

#### Exclusion criteria

Participants will be excluded if they suffer from serious medical conditions, such as uncontrolled hypertension, diabetes mellitus requiring insulin injection, past or current malignant tumour, severe dyslipidaemia, liver or kidney dysfunction, anaemia, active pulmonary tuberculosis, or other infectious or systemic diseases inappropriate for treatment with acupuncture.

Participants will not be eligible if they have congenital nasal abnormalities, sinusitis, active asthma, a history of nose surgery, received systemically administered corticosteroids within six months prior to enrolment, or received alternative and complementary treatment, (i.e., acupuncture or herbal medication) for AR within the previous six months. Typical oral and nasal H1 blockers, intranasal/oral corticosteroids, or nasal anti-cholinergic medication will be stopped at least one week before enrolment. OTC drugs will be allowed for managing episodic colds, headaches, dyspepsia, etc. However, participants will be asked to disclose all medication use prior to enrolment. OTC drugs containing an H1 anti-histamine or anti-cholinergic component will not be allowed, since they may directly affect nasal symptoms. We will record the drugs taken by each participant at every visit, and participants will be requested to notify us of any change to their medication/supplement regimen. Additional acupuncture treatments, herbal prescriptions, or therapeutic intervention by other clinicians will not be allowed during the treatment period. Participants in the waitlist group will not receive acupuncture or sham acupuncture treatments during the study. After four weeks, if participants elect to try the acupuncture treatment, the real acupuncture treatment will be provided.

### Acupuncture treatment protocol

#### Acupuncture intervention and sham acupuncture

Acupuncture will be performed by certified acupuncture medical doctors at four centres. Qualified specialists of acupuncture in traditional Korean or Chinese medicine with at least three years of clinical experience will perform the acupuncture in this study. All treatment regimens will be standardised between Korean and Chinese practitioners *via *video and international workshops. Participants will be randomly assigned to the active acupuncture group, the sham acupuncture group, or the waitlist group. The active acupuncture and sham acupuncture group participants will receive real and sham acupuncture treatments respectively, three times/week for a total of 12 sessions over four weeks. A 0.20 mm (diameter) × 30 mm (length) disposable needle (Dongbang Acupuncture Inc, Korea) will be used. For the active acupuncture group, 10 acupuncture points (bilateral LI4, LI20, ST2, and ST36, unilateral EX-1 and GV23) according to 'WHO Standard Acupuncture Point Location' [18] were selected for use based on an expert discussion held in Beijing in December, 2008. These acupuncture points were selected according to traditional Chinese medicine (TCM) theory, which is quite different from that of conventional medicine. Briefly, the basic therapeutic strategies of acupuncture, based on a meridian system, is to correct the body's core imbalances in order to disperse blocked *Qi *and blood in treating disease [19]. According to the TCM theory, when an acupuncture point is stimulated, treatment effects tend to occur in specific parts of the body along the meridian that contains this specific acupuncture point. There are two categories of acupuncture points used to effectively regulate *Qi *and blood for syndromes: local points and distal points. In establishing an acupuncture strategy for this study, we focused on the imbalance of the Large Intestine and/or Stomach meridian and/or Governor Vessel due to an invasion of pathogenic agents, such as cold, wind, and damp, as the key pathogenesis of PER. These three key meridians associated with PER flow together through the nose, and are therefore closely connected with respiratory function. In order to disperse pathologic *Qi *and blood from these meridians and improve the function of the nose and sinuses, the local or adjacent points, including LI20 in the Large intestine meridian, ST2 in the Stomach meridian, GV23 in the Governor vessel and EX1, were selected. The remote points, including LI4 and ST36, were selected to correct the imbalance of the relevant meridians and organs. LI4 was selected for lung *Qi *deficiency syndrome, and ST36 for spleen *Qi *deficiency syndrome. These two syndromes represent the pathologic basis of PER in TCM theory.

As for treatment sessions, previous high quality trials [14,16] used a total of 16 acupuncture sessions, twice a week for eight weeks. But those trials allowed the concomitant use of conventional medication for symptomatic relief of AR, so interpretation of the efficacy of acupuncture is limited. In contrast to those studies, we added one additional session of acupuncture treatment per week (i.e., three times/week) without allowing PER symptom relievers; this addition was thought to compensate for the reduced effect of not using conventional medication. As with treatment duration, we considered four weeks to be a sufficient period of time to obtain clinically relevant improvement based on clinical experiences with PER patients. The needles will be inserted to a depth of 7–30 mm, depending on the points selected. In order to achieve *de-qi *sensation for real acupuncture treatment, the needles will be manually manipulated and maintained for 20 minutes, with manual stimulations at the start and just before the withdrawal of needles. Additional interventions, such as infrared irradiation or electronic stimulation, will not be allowed during acupuncture treatment. For real acupuncture treatment, needles will be inserted into the aforementioned acupuncture points at an appropriate insertion angle and direction (Table 1). For example, at EX1, the needle will be inserted to a depth of 20 to 30 mm in an oblique direction towards the nose with respect to the skin. Each needle will be rotated until the participant and doctor feel de-qi sensations. For the sham acupuncture treatment, the needles (the same type used for the active acupuncture treatment) will be inserted at non-acupuncture point sites, 1 – 1.5 cm from the acupuncture points. However, they will be inserted to a depth of 3 – 5 mm perpendicularly to the skin, using a hollow pool and a shallow needling technique to avoid de-qi. The needle will then be rotated once in order to preserve patient blinding. The duration of this procedure will be the same as the real acupuncture treatment.

**Table 1 T1:** Acupuncture points and needling procedure for real and sham acupuncture.

Real Point	Angle and Direction	Depth (mm)	Sham point
LI20 (Both)	Obliquely along the nasolabial sulcus towards the root of nose with respect to the skin	20–30	Lateral 1.5 cm and Downward 1 cm to LI20.

ST2 (Both)	Transversely, upward to the centre of the pupil with respect to the skin	7–10	Lateral 1.5 cm to ST2

EX1 (unilateral)	Transversely, downward to the nose	20–30	Upward 1.5 cm, Rt. Lateral 1 cm to EX1

GV23 (unilateral)	Transversely, downward to the forehead with respect to the skin	20–30	Rt. Lateral 1 cm to GV23

LI4 (Both)	Perpendicular to the skin	20–30	Posterior to the web margin between the first and second phalanges

ST36 (Both)	Perpendicular to the skin	20–30	Medial 1.5 cm to ST36

In the sham acupuncture procedure, the needle will be inserted at each sham point to a depth of 3–5 mm, perpendicular to the skin, using a needle tube with a one-time rotation

Needle sites in both active and sham acupuncture groups will be swabbed with 2% boric acid before insertion. On withdrawal of the needle, dry sterilised cotton balls will be firmly applied to the insertion points. Blood pressure will be measured before and after acupuncture treatment. Before acupuncture, each participant will be evaluated by an assessor blinded to participants' random allocation, and their symptoms and total non-nasal symptom scores will be recorded. The level of any discomfort in the acupuncture or sham acupuncture will also be monitored.

